#### Collection of clinical results

We will obtain the results of any subsequent cervical cytology, colposcopy, and histology from the NCSP-Register or GPs, ISPs, Māori/Pacific/Asian Providers, and DHB colposcopy services in order to determine prevalence of cervical abnormalities.

### Data entry, management and security

A bespoke secure online database has been created to manage details of responding and non-responding participants. Access databases will be developed for data entry from the study questionnaires. Any specimen taken for screening as part of the study is reported to the NCSP-Register by direct laboratory notification.

An internal data safety monitoring committee has been established (public-health physician; molecular HPV expert; general practitioner; colposcopist; nurse smear-taker; research nurse; epidemiologist) to assess and evaluate any clinical concerns or serious adverse events occurring in the study.

### Statistical analysis

The main analyses will focus on the primary outcome of the study: participation, i.e. the proportion of women who provide a self-sample compared with the proportion who attend for cytology, stratified by ethnicity. These will initially be assessed simply by comparing (with Chi-square tests) the proportions who participated in each group; this will be followed by a mixed model multiple logistic regression analysis to adjust for potential confounders (e.g. age, ethnicity, screening history, socioeconomic status) and to assess which factors (in addition to the intervention) affect participation. The same analyses will be repeated separately for both un- and under-screened women, providing important information on whether screening history affects participation.

We will also analyse the prevalence of oncogenic HPV types in participating women in the self-sampling groups, and the prevalence of cervical abnormalities in participating women in the cytology group. Prevalence odds ratios [51] will be calculated using logistic regression and compared across ethnicities, adjusting for age.

Secondary analyses will assess the association between acceptance of self-sampling and demographic and other factors. For comparisons across ethnicity and screening-history (un- and under-screened) groups, logistic regression will be used, adjusting for age and other potential confounding variables. Time for return of sample will be calculated for self-sampling groups as a policy-relevant indicator of courier reliability; laboratory turnaround time and proportion of unsatisfactory samples will be monitored.

Experience of the test, enablers/barriers of screening, and factors associated with screening preferences will be described for each group (mail-out or clinic-based), by ethnicity and demographic factors. Standard descriptive statistical methods will be used. T-tests and Chi-square tests will be used to assess statistical significance. Multiple linear or logistic regression (as appropriate) will be used to compare these responses between the two groups (mail-out or clinic-based), adjusting for potential confounders.

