**Fig. 1 Fig1:**
[figure not shown]
Study design overview

Women will be individually randomised 3:3:1 to the study arms: clinic-based self-sampling in which women are invited to take a self-sample at their usual general practice (GP); mail-out self-sampling in which women are mailed a kit and invited to take a self-sample at home; and usual care in which women are invited to attend a clinic for a standard cytology sample (attendance assessed through the NCSP-Register and GP records). We aim to randomise approximately equal numbers of women from each ethnic group to each of the study arms. There is also a nested “opportunistic” sub-study at most clinics, where women who have not responded within 3 months to their study invitation are offered, at any subsequent visit to their clinic (as suggested in Arbyn et al [27] and Lim and Sasieni [39]), either self-sampling in the clinic or the option of having a sampling kit mailed to their home. This sub-study will enable us to describe policy-relevant findings including those that inform the practical implementation of an opportunistic offer of HPV self-sampling in a clinic situation.

An overview of the schedule of enrolment, interventions, and assessments is provided in Table 1.

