### Sample size

We aim to invite a minimum of 3550 un- or under-screened (≥5 years overdue) Māori, Pacific and Asian women (1050, 1250, 1250 respectively) for screening. The invitation numbers are pragmatically based on the number of eligible women in the region and study resources. With 450 Māori women invited in both the clinic and mail-out self-sampling groups we will have > 95% power to detect a 10% difference in uptake between the groups (e.g.*,* 15% uptake in the clinic group and 25% in the mail-out group). With 450 Māori women invited in the clinic self-sampling group and 150 Māori women invited in the usual care group we will have > 85% power to detect a 10% difference in uptake between the groups (e.g.*,* 15% uptake in the clinic group and 5% in the usual care group).

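### Repeating the analyses separately in un-screened and under-screened women shows neither whether screening history affects participation nor whether it changes the intervention effect; the second question needs an arm-by-history term, and none is stated

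*Protocol article*

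**What the plan says.** The Statistical analysis section of the protocol article sets the primary comparison as "the proportion of women who provide a self-sample compared with the proportion who attend for cytology, stratified by ethnicity". Chi-square tests come first. A mixed logistic regression follows, to "adjust for potential confounders (e.g. age, ethnicity, screening history, socioeconomic status") and to see which factors besides the intervention affect participation. Screening history therefore enters the pooled model as a covariate.

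The section then adds: "The same analyses will be repeated separately for both un- and under-screened women, providing important information on whether screening history affects participation".

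Under secondary analyses of acceptance of self-sampling it states: "For comparisons across ethnicity and screening-history (un- and under-screened) groups, logistic regression will be used, adjusting for age and other potential confounding variables". No arm-by-screening-history or arm-by-ethnicity term is named anywhere in the section.

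The Methods/design section states the allocation: "Women will be individually randomised 3:3:1 to the study arms". The Sample size section gives the ethnic group sizes, "Māori, Pacific and Asian women (1050, 1250, 1250 respectively) for screening", and supports power only within Māori women, where usual care has "150 Māori women invited in the usual care group". It does not state alpha or the proportions of un-screened and under-screened women.

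**The concern.** The plan names a method and the inference it is meant to serve, and the two do not match on either reading.

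- *Does history affect participation?* This is a comparison between the two history groups. An analysis confined to one group holds history fixed and cannot estimate its effect. The pooled model, with history as a covariate, can.
- *Does history change the intervention effect?* This is the natural purpose of repeating the arm comparisons by group, but two separate tests do not compare two effects. One p-value below 0.05 and one above can easily arise from the same true effect when the groups are small.

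The trial is meant to inform national screening policy. A statement that self-sampling works in never-screened but not in under-screened women, or the reverse, could influence who is offered it, so the comparison behind such a statement should be a valid one.

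**Working it through.** **Inputs.** From Sample size: 450 clinic, 450 mail-out and 150 usual care for Māori women; example uptake of 5% (usual care), 15% (clinic) and 25% (mail-out). From the 3:3:1 ratio: Pacific or Asian, 1250 × 3/7 ≈ 536 per self-sampling arm and 1250/7 ≈ 179 usual care; all women, 3550 × 3/7 ≈ 1521 and 3550/7 ≈ 507. Assumptions: two-sided alpha 0.05; a 50:50 split of history, varied to 90:10.

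**Formula.** With p̄ the pooled proportion, power = Φ{(|p1 − p2| − 1.96·√[p̄(1 − p̄)(1/n1 + 1/n2)]) / √[p1(1 − p1)/n1 + p2(1 − p2)/n2]}.

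**The plan's own figures.**
- Mail-out vs clinic, 450 vs 450, 25% vs 15%: Φ[(0.10 − 0.0523)/0.0265] = 96.4%, in agreement with the stated > 95%.
- Clinic vs usual care, 450 vs 150, 15% vs 5%: Φ[(0.10 − 0.0611)/0.0245] = 94.4%, consistent with the stated lower bound of > 85%.

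**Same true effect in both history groups.** Let a and b be the power in each group. The groups are independent, so P(exactly one significant) = a(1 − b) + b(1 − a).

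Māori, clinic vs usual care, 50:50, so 225 vs 75 per group: Φ[(0.10 − 0.0864)/0.0346] = 65.2%, and 2 × 0.652 × 0.348 = 45%.

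At 50:50:

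| Women | Clinic vs usual care, 15% vs 5% | Mail-out vs clinic, 25% vs 15% | Mail-out vs usual care, 25% vs 5% |
|---|---|---|---|
| Māori | 45% (power 65% per group) | 37% (76%) | 1% (99%) |
| Pacific or Asian | 38% (74%) | 29% (83%) | 0.3% (99.9%) |
| All 3550 | 0.5% (99.8%) | 0.3% (99.8%) | < 0.1% |

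Uneven splits, clinic vs usual care:
- Māori: 48% at 60:40; 57% at 70:30 (0.821 × 0.602 + 0.398 × 0.179); 69% at 80:20.
- All women: 1%, 5% and 19% at the same splits, and 55% at 90:10.

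**Interaction test on the same data.** In 200,000 simulated trials (15% vs 5% in both groups, 50:50), a Wald test of the difference in log odds ratios rejected in 1.7% (Māori), 2.1% (Pacific or Asian) and 4.2% (all women). In the same simulations exactly one group was significant in 43%, 36% and 0.5%.

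**Precision of the comparison that is needed.** For clinic vs usual care at 50:50, the variance of the risk difference in each Māori history group is 0.1275/225 + 0.0475/75 = 0.0012. The difference between the two groups' effects has SE √0.0024 = 0.049, a 95% CI half-width of 9.6 percentage points, about as large as the 10-point effect itself. For all women (761 vs 254 per group) the variance is 0.000355, the SE √0.00071 = 0.0266 and the half-width 5.2 points.

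**The case against.** The best defence has four parts.

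1. The sentence speaks of history affecting participation, not of effect modification, and no rule says that significance in one group only will be read as a differing effect. This stands. A reader might infer that policy would follow whichever group reaches p < 0.05; nothing in the article says so. The discordance figures measure the risk of a misreading that the plan leaves open, not a planned decision rule.
2. Other planned analyses already compare the groups. The pooled model gives main effects of history and ethnicity, and the secondary logistic regression compares history groups on acceptance. This also stands, so it would be wrong to say that there is no joint model for ethnic differences in participation. But neither analysis is stated to compare the arm effect between groups.
3. A reader might see a contradiction in stratifying by ethnicity and also adjusting for it. There is none: ethnicity-specific comparisons followed by a pooled adjusted model are compatible.
4. Interaction terms are commonly left to an analysis plan. That would be an answer if the article were silent. It is not: it names separate analyses and says what they will show.

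An interaction test also has limits. In the small groups it is conservative (1.7% against a nominal 5%) and imprecise, and its answer depends on whether effects are measured as odds ratios or risk differences.

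**Conclusion.** The point holds as a mismatch between a stated method and its stated purpose. The primary arm comparison is unaffected.

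The size depends on the contrast and on how far the data are divided. At an assumed 50:50 split and two-sided alpha 0.05, with identical true effects, the chance of significance in one history group only, within one ethnic group, is 38–45% for clinic versus usual care and 29–37% for mail-out versus clinic. It is about 1% or less for mail-out versus usual care, and about 0.5% for clinic versus usual care in all 3550 women. Uneven splits raise it, to 57% for Māori clinic versus usual care at 70:30 and 55% for all women at 90:10.

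A reader might take roughly even odds of a spurious finding as the general figure. The documents do not support that: it fits some contrasts within one ethnic group, or a very uneven split, and the article does not report the split.

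**What to change.** In the Statistical analysis section:

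- Let the main effect of screening history in the planned mixed logistic model answer whether history affects participation.
- Add an arm-by-screening-history term to that model, and an arm-by-ethnicity term if effects are to be compared across ethnic groups.
- Report participation differences between arms within each history group, with 95% CIs, as description.
- Base any claim that the effect differs on the interaction estimate and its CI, and state the scale (odds ratio or risk difference).

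The cost is a few lines of analysis wording; no further data or participants are needed. The downside is low power for the interaction in small groups, so the text should also say that a non-significant result does not show equal effects.

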### Sample size

We aim to invite a minimum of 3550 un- or under-screened (≥5 years overdue) Māori, Pacific and Asian women (1050, 1250, 1250 respectively) for screening. The invitation numbers are pragmatically based on the number of eligible women in the region and study resources. With 450 Māori women invited in both the clinic and mail-out self-sampling groups we will have > 95% power to detect a 10% difference in uptake between the groups (e.g.*,* 15% uptake in the clinic group and 25% in the mail-out group). With 450 Māori women invited in the clinic self-sampling group and 150 Māori women invited in the usual care group we will have > 85% power to detect a 10% difference in uptake between the groups (e.g.*,* 15% uptake in the clinic group and 5% in the usual care group).

### Ethical and cultural considerations

The study has been approved by the New Zealand Northern B Health and Disability Ethics Committee (HDEC) (reference: 17/NTB/120). The New Zealand Ministry of Health (including the National Kaitiaki Group) and the participating DHBs, PHOs, and primary-care clinics have all given approval for the use of data to identify and contact eligible women.

There are a range of ethical and cultural issues in this study. The issues include informed consent, privacy and confidentially, language barriers (especially for Pacific and Asian women), health literacy and awareness of screening, sampling and storage of tissue, data ownership, and that for some women (especially Māori women) the genital area is considered tapu (sacred/forbidden/taboo). Whakamā (embarrassment/reticence/shyness) may be an issue for some women in this study, and appropriate ways to approach women will be co-designed with each provider; a range of strategies are likely to be required. There is also the issue of potential stigmatisation (e.g. a deficit focus for un-screened/under-screened women); however, this study seeks a strength-based approach of enabling women to access a novel technology to enhance their wellbeing. Our research group includes substantial research expertise with Māori health, Māori research methodology, and research with women, screening, and in cervical screening specifically. The study has an advisory group structure for each of the study populations: Māori, Pacific and Asian.

## Discussion

The success of cervical-cancer screening in New Zealand is limited by incomplete participation, particularly amongst Māori, Pacific and Asian women. More than half of the invasive cervical cancer cases among these populations occur in those who have not attended cervical screening [5]. Improving participation rates and reducing outcome inequities are priorities for New Zealand’s health system. The longstanding nature of these problems shows that new strategies are needed. HPV self-sampling may improve the participation rates in groups of women who are underserved by current screening programmes that require a clinician-collected sample [34]. However, it is important to assess the acceptability and optimal invitation approaches for self-sampling in New Zealand in order to provide the country-specific evidence needed to inform policy. The current trial will provide robust evidence on whether HPV self-sampling could be used to increase cervical screening participation rates in un- and under-screened Māori, Pacific, and Asian women. This trial is the first to evaluate the effectiveness of mailed self-sampling for cervical-cancer screening in New Zealand, and one of the first internationally to evaluate the effectiveness of opportunistic in-clinic invitations for self-sampling.

## Data Availability

Anonymized data and biological samples will be collected during the trial and used only for the analysis declared in the study protocol. The availability of the data that will be collected as part of this study is being confirmed.

## Abbreviations

ANZCTR: Australian and New Zealand Clinical Trials Registry
ASC-H: Atypical squamous cells - cannot exclude high-grade squamous intra-epithelial lesion
ASC-US: Atypical squamous cells of undetermined significance
CIN2 +: Cervical intraepithelial neoplasia grade two or higher
CIN3+: Cervical intraepithelial neoplasia grade three or higher
DHB: District Health Board
DNA: Deoxyribonucleic acid
GP: General Practice
HDEC: Health and Disability Ethics Committee
HPV: Human papillomavirus
HSIL: High-grade squamous intra-epithelial lesion
ISP: Independent Service Providers
LBC: Liquid-based cytology
LSIL: Low-grade squamous intra-epithelial lesion
NCSP: New Zealand National Cervical Screening Programme
PCR: Polymerase chain reaction
PHO: Primary Health Organisation
US FDA: United States Food and Drug Administration
